## Abstract

**Background:**

More than 50 percent of all infants born very preterm will experience significant motor and cognitive impairment. Provision of early intervention is dependent upon accurate, early identification of infants at risk of adverse outcomes. Magnetic resonance imaging at term equivalent age combined with General Movements assessment at 12 weeks corrected age is currently the most accurate method for early prediction of cerebral palsy at 12 months corrected age. To date no studies have compared the use of earlier magnetic resonance imaging combined with neuromotor and neurobehavioural assessments (at 30 weeks postmenstrual age) to predict later motor and neurodevelopmental outcomes including cerebral palsy (at 12–24 months corrected age). This study aims to investigate i) the relationship between earlier brain imaging and neuromotor/neurobehavioural assessments at 30 and 40 weeks postmenstrual age, and ii) their ability to predict motor and neurodevelopmental outcomes at 3 and 12 months corrected age.

**Methods/design:**

This prospective cohort study will recruit 80 preterm infants born ≤30 week’s gestation and a reference group of 20 healthy term born infants from the Royal Brisbane & Women’s Hospital in Brisbane, Australia. Infants will undergo brain magnetic resonance imaging at approximately 30 and 40 weeks postmenstrual age to develop our understanding of very early brain structure at 30 weeks and maturation that occurs between 30 and 40 weeks postmenstrual age. A combination of neurological (Hammersmith Neonatal Neurologic Examination), neuromotor (General Movements, Test of Infant Motor Performance), neurobehavioural (NICU Network Neurobehavioural Scale, Premie-Neuro) and visual assessments will be performed at 30 and 40 weeks postmenstrual age to improve our understanding of the relationship between brain structure and function. These data will be compared to motor assessments at 12 weeks corrected age and motor and neurodevelopmental outcomes at 12 months corrected age (neurological assessment by paediatrician, Bayley scales of Infant and Toddler Development, Alberta Infant Motor Scale, Neurosensory Motor Developmental Assessment) to differentiate atypical development (including cerebral palsy and/or motor delay).

**Discussion:**

Earlier identification of those very preterm infants at risk of adverse neurodevelopmental and motor outcomes provides an additional period for intervention to optimise outcomes.

**Trial registration:**

Australian New Zealand Clinical Trials Registry ACTRN12613000280707. Registered 8 March 2013.

**Electronic supplementary material:**

The online version of this article (doi:10.1186/s12887-015-0439-z) contains supplementary material, which is available to authorized users.

## Background

Infants born very preterm (<32 weeks gestational age; GA) are at a high risk of experiencing significant motor difficulties with 10–15 % developing cerebral palsy (CP) [1], a further 40–50 % having minor motor and behavioural difficulties [2, 3] and 30–60 % experiencing cognitive difficulties at school age [4]. At least 25 % of infants follow a trajectory of typical development with no evident sequelae of their difficult neonatal course [5]. Interventions are becoming available which aim to improve outcomes for infants born very preterm, necessitating the development of tools which can firstly identify those infants at risk of adverse outcomes as early as possible, and secondly provide accurate quantitative measurement of changes that are the result of an intervention. Currently, brain Magnetic Resonance Imaging (MRI) at term equivalent age (TEA) combined with the General Movements assessment (GMs) at 3 months corrected age (CA), show the greatest predictive accuracy of motor and neurodevelopmental outcomes and CP at 1, 2 and 5 years CA [6–10].

In preterm infants imaged at TEA, structural MRI (T1 and T2 weighted images) analysed qualitatively for evidence of white and grey matter abnormalities predict motor and cognitive outcome [8, 11], motor distribution of CP [12, 13], severity of motor involvement in CP [14] and neurobehavioural development [15]. White matter injury has been identified as the predominant injury in the preterm infant brain, with lesions such as periventricular leukomalacia (PVL) and intra-ventricular haemorrhage (IVH) well described and linked to poorer outcomes and CP [8, 16]. More recently, recognition of the intercurrent and subsequent developmental disturbances in both white and grey matter as a result of the primary lesion, support the description of preterm brain injury as an ‘encephalopathy of prematurity’ [17]. Qualitative classification of grey and white matter macrostructure from structural MRI has improved prediction of outcomes, but the need for quantitative microstructural information has lead to investigation of diffusion MRI in this population [18, 19].

Diffusion MRI measures the random motion of water molecules, which is hindered and restricted by the presence of cell membranes, the cytoskeleton, and macromolecules in the brain [20]. A number of quantitative metrics can be obtained from diffusion MRI to characterise the tissue, including fractional anisotropy (FA), mean diffusivity (MD), axial diffusivity (AD), and radial diffusivity (RD) derived using the diffusion tensor model (i.e. Diffusion Tensor Imaging, DTI) [21]. These measures of the degree of restriction of diffusion (FA) and speed of diffusion (MD) change during brain development due to increasing fibre organisation, membrane proliferation, and myelination [22]. Diffusion MRI also provides estimates for the direction of the underlying white matter tracts, and, using tractography, enables the delineation of those pathways as they course through the brain.

White matter damage of prematurity is associated with increased values of MD and decreased values of FA [22, 23]. A significant correlation exists between values of FA in the corticospinal tracts and postmenstrual age (PMA) [24] and between MD and later motor impairment [25]. Higher MD values at term are associated with poorer neurodevelopmental outcomes at 2 years in preterm infants [26]. Diffusion MRI has been reported to be an independent predictor of psychomotor delay [25] and to predict CP with a sensitivity of 80 % (95 % Confidence Interval [CI] 28–100) and a specificity of 66 % (95 % CI 53–78) [25]. Associations between FA values and cognitive outcomes have been reported [27]. The use of MRI tractography to predict neurodevelopmental outcomes is not yet well established [28].

Potential limitations of diffusion imaging such as complex crossing fibre microstructure, reliability and reproducibility, are being addressed through novel diffusion MRI acquisition and analysis techniques [29]. Customized for preterm babies, they include novel pre-processing, the use of 60-direction High Angular Resolution Diffusion Imaging (HARDI), high b values and fibre orientation distribution analysis [30]. These deal with the identified need for greater accuracy of tractography and improved quantitative markers [31].

Imaging technology advances are now able to be coupled with earlier imaging, with the advent of MRI compatible incubators. Safety and feasibility have been established for MRI in the neonatal period after birth and before TEA, with the potential to provide further insights into this period of rapid brain development [32–37]. At the stage very preterm infants enter the extra-uterine environment, between the end of the second and beginning of the third trimesters, cortical neurogenesis and migration are complete, axonal and dendritic branching continue vigorously, and synaptogenesis is commencing [38, 39]. From this stage until TEA is reached, white matter increases by 5 times the original volume, cortical grey matter volume increases 4 times and cortical folding both commences and is essentially completed [15, 40]. Brain development is rapid, vulnerable to injury but also adaptive to environmental inputs that guide and consolidate developing brain connections in a process termed neuroplasticity [41].

An area of specific interest in early imaging is the cortical subplate [42]. This structure consists of neurons formed in deep grey matter neurogenic sites such as the thalamus, and arrive to lie below the cortical neurons that migrated earlier from the subventricular zone [43]. At 30 weeks gestation, the subplate reaches its peak thickness, many times thicker than the cortex, and by term has almost completely regressed [44]. This major wave of growth and death establishes the long range projections between the deep grey matter and the cortex, and the short- and long- range cortico-cortical connections that are fundamental to integration of motor and cognitive functions [45]. This information on brain structure and structural connectivity from earlier neuroimaging increases the potential of understanding the trajectory of structural brain development.

Electroencephalography (EEG) is a useful method of measuring cortical function for diagnosis and predicting later outcomes. Relationships between EEG and structural and functional connectivity have been shown throughout development in both adults and infants [46–50]. Electroencephalography signals represent cortical electrical activity measured on the scalp and can be collected non-invasively with relative ease and low cost. Electroencephalography has strong predictive capacity for outcome in the term infant with hypoxic ischaemic encephalopathy [51]. Increasing use in the preterm population, particularly in configurations using a limited number of electrodes, are evidenced with the first reports of its utility in predicting outcome [52, 53]. Multi-channel EEG, typically 10–20 channels in the newborn, is well established in clinical practice and provides information about normal and abnormal functionality of the developing brain [54]. Deeper insights are possible with further analysis of multichannel EEG [55–58]. The power and the frequency of oscillations in the cortex can be assessed using power spectral density analysis [59].

Electroencephalography is able to define the electrical activity of the neonatal brain structural network that is visualised in diffusion imaging [30, 60, 61]. The electrical activity of these networks is characterised by two alternating modes observed in the amplitudes of EEG signals: a mode associated with the self-organising, locally generated spontaneous electrical activity transients (SATs) and a mode representing the low-amplitude intervals between SATs [62, 63]. This bimodality gradually attenuates from mid gestation and activity becomes continous by term [63].

In parallel to neuroimaging and neurophysiological modalities, several clinical assessments of neuromotor, neurobehaviour and neurological function are proposed for use in the preterm period and early infancy [64]. Two systematic reviews on the clinimetric properties of such measures found Prechtl’s General Movements Assessment to have the greatest predictive accuracy of an outcome of CP [64, 65]. This neuromotor assessment evaluates spontaneous infant movement from preterm birth until 5 months CA [66]. A systematic review examining the accuracy of tests to predict CP included a meta-analysis of GMs and reported a pooled sensitivity and specificity of 98 % (95 % CI 74–100 %) and 91 % (95 % CI 83–93 %) respectively [10]. It is important to note that GMs at 3 months CA also predict severity of CP [67], cognition [68], minor neurological dysfunction [69] and behavioral and psychiatric outcome [70].

Neurobehaviour refers to an infant’s ability to self-regulate, orientate, be responsive to stimuli and sustain attention [71]. Neurobehavioural assessment in the preterm period reveals changes between birth and TEA, and differences between preterm and term infants assessed at TEA [72, 73]. Poorer neurobehavioural performance at TEA is associated with white matter abmormality on structural MRI, a range of adverse perinatal variables and predicts neurodevelopmental outcomes and CP at 18 months CA [72, 74, 75]. Components of the NICU Neonatal Neurobehavioural Scale, namely a low handling score, low movement score and high lethargy score are significantly related to an outcome of CP [75].

Neurological examination of infants offers reasonable prediction of outcomes, with sensitivity and specificity increasing as the infant progresses from the preterm period, through TEA and into the first year of life [10, 76]. Prediction of CP and motor outcome in the preterm period is relatively poor due to the presence of early transient abnormal signs with later good outcomes causing false positives and the converse resulting in false negatives [10, 77]. When neurological examination is performed before term age in preterm infants, the sensitivity for an outcome of CP is 57–86 % and specificity 45–83 % [78, 79]. At term, neurological assessment has a sensitivity of 88 % and specificity of 46 % to predict structural MRI abnormalities [80] and 68–79 % and 63–70 % to predict CP [78, 81]. In the post term period sensitivity and specificity range from 68–96 % and 52–97 % respectively [78, 81].

Perinatal factors, including growth and nutrition, have been identified as risk factors of adverse outcomes. Poor growth during the first weeks after preterm birth is a significant predictor of poor neurodevelopmental outcome [82–84]. Increased nutrient intake leads to better growth [85–87], and presumably better brain development, although this relationship is not proven. There is a need for clear evidence of the relationship between early nutrient intake and brain development in preterm infants, so that improved nutrient regimens can be designed.

Individual modalities of MRI, EEG, clinical measures, perinatal risk factors and nutrition have been evaluated in relation to later outcomes for preterm infants as described above. Combinations of modalities have been evaluated and often demonstrate improved prediction of outcomes over individual modalities alone [7, 6, 10, 88, 89]. The relationships between modalities at TEA are emerging, but to our knowledge, few studies to date have examined the relationships between early clinical measures, perinatal risk factors and nutrition, and very early imaging at 30 weeks PMA [7, 15, 72, 73, 80, 90–92]. This study aims to contribute to the understanding of brain structure-function relationships in the very early phase of the developmental trajectory, improving the ability to identify infants at risk of adverse outcomes, facilitating innovation of interventions and developing quantitative biomarkers of brain development.

### Broad aim

This prospective cohort study of infants born ≤30 weeks will investigate the relationship between brain structure (structural and diffusion MRI), brain function (neurological, neuromotor, neurobehaviour, vision and EEG), perinatal risk factors and nutrition of very preterm infants in the preterm period (30–32 weeks) and at TEA; then examine the ability of these early measures to predict motor and neurodevelopmental outcomes at 3 and 12 months CA.

### Primary aims

In a prospective cohort study of infants born at ≤30 weeks, and a term reference group, this study aims:To examine the relationship between brain structure on structural and diffusion MRI, brain function on clinical measures of neurological, neuromotor and neurobehavioural performance, and perinatal risk factors at 30 and 40 weeks PMA.To determine whether brain structure and function at 30 weeks PMA predicts outcomes of brain structure and function at 40 weeks PMA, 3 months CA and 12 months CA.To evaluate the ability of structural and diffusion MRI and functional measures at 30 and 40 weeks PMA age to predict motor outcome at 3 months CA and motor, neurodevelopmental outcome and CP at 12 months CA.To evaluate the ability of perinatal variables and social risk (socio-economic status; SES) to predict severity of motor outcome and CP at 12 months CA.

### Secondary aims

To examine the development of motor, sensory, visual and auditory connectivity between 30 week and 40 week MRIs in infants born preterm with and without brain lesions.To examine the correlation between brain function on dense array EEG, and motor and visual outcomes at 40 weeks PMA.To evaluate the ability of dense array EEG at 40 weeks PMA to predict visual outcome at 3 months CA and cognitive outcome at 12 months CA.To examine the correlation between data fusion of brain functions on dense array EEG and brain structure on diffusion MRI, and motor and visual outcomes at 40 weeks PMA.To evaluate the ability of data fusion of brain functions on dense array EEG and brain structure on diffusion MRI, to predict visual outcome at 3 months CA and cognitive outcome at 12 months CA.To examine the relationship between preterm macronutrient intake from birth to 34 weeks and brain development at 40 weeks PMA, and determine if nutritional intake is more predictive of brain development than other maternal and neonatal risk factors.

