### Data analysis and statistical considerations

When models involve brain structure and function data from one time point (either 30–32 or 40–42 weeks), standard regression models will be constructed; when models use data from both 30–32 and 40–42 weeks, mixed-effects models that take into account within-infant correlation will be used. Models will be constructed using standard principles; first univariable analyses will be used to identify variables significant at the *p* < 0.15 level and these variables then entered into multivariable models one-by-one, in decreasing order of significance. At each step the current model will be compared to previous models using the likelihood ratio test. Linear regression will be used for continuous outcomes (e.g. diffusion MRI measures of FA and MD); logistic regression for binary outcomes (e.g. disability/no disability); and multinomial logistic regression for categorical outcomes with > 2 categories (e.g. NSMDA categories of normal/suspect/abnormal). Results will be presented as effect estimates and 95 % confidence intervals. The sensitivity and specificity of the predictive assessment model will be determined based on diagnosis of disability using standard definitions. Perinatal, clinical, demographic and social characteristics will be included as covariables when appropriate. Analyses will be supervised by [name], a senior biostatistician at The University of Queensland.

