## Discussion

To our knowledge, this protocol describes the first study examining the clinical correlates of early advanced brain imaging and clinical measures at 30 weeks PMA to predict motor and neurodevelopmental outcomes at 3 and 12 months CA.

The results of this study will i) establish the relationships between early clinical measures, EEG, perinatal variables and nutrition and early advanced neuroimaging at 30 weeks PMA, ii) establish which components of brain structure and function most accurately predict neurodevelopmental, motor outcomes and CP at 3 and 12 months CA, iii) accurately identify infants at risk of adverse outcomes at an earlier stage, introducing an additional window of opportunity for intervention, iv) contribute to understanding brain development between 30 and 40 weeks PMA, v) and develop robust quantitative biomarkers of brain maturation, which can then be used in the research of interventions in this population.

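### Secondary aim 6 and the Discussion promise a ranking of predictors, but the only model-building analysis described tests each predictor against zero and estimates no difference between predictors

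*Protocol article*

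**What the plan says.** Two places in the protocol article set a comparative goal.

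- **Secondary aims, last item.** After relating macronutrient intake from birth to 34 weeks to brain development at 40 weeks PMA, the study will "determine if nutritional intake is more predictive of brain development than other maternal and neonatal risk factors".
- **Discussion.** The results will "establish which components of brain structure and function most accurately predict neurodevelopmental, motor outcomes and CP at 3 and 12 months CA".

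The model building is in *Data analysis and statistical considerations*.

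- **Screen:** "first univariable analyses will be used to identify variables significant at the *p* < 0.15 level".
- **Entry:** "these variables then entered into multivariable models one-by-one, in decreasing order of significance".
- **Test:** "At each step the current model will be compared to previous models using the likelihood ratio test". No significance level is given for this test.
- **Reporting:** "Results will be presented as effect estimates and 95 % confidence intervals".
- **Accuracy:** "The sensitivity and specificity of the predictive assessment model will be determined based on diagnosis of disability using standard definitions".

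The model is linear regression for continuous outcomes, logistic for binary and multinomial for categorical.

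**The concern.** To say that nutrition is more predictive than another risk factor is to reject equality of their predictive value. The described steps test other nulls: that a variable has no effect alone (the screen), or that it adds nothing to those already entered (the likelihood ratio test). The planned intervals are for individual effects. Sensitivity and specificity describe the predictive model as a whole, not rival components.

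Order of entry matters as well. The variable with the smaller p-value enters first. A correlated rival must then show added value, a requirement the first entrant never faced. The article itself gives reason to expect correlated predictors. *Perinatal data collection* defines proven necrotising enterocolitis by treatment that includes nil by mouth, which is tied to intake, and the first hypothesis expects strong correlation among MRI, clinical and perinatal measures at 30 weeks.

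At stake is a statement that nutrition does, or does not, outperform gestation or illness when the data do not separate them. The Background wants evidence on nutrient intake so that improved regimens can be designed.

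**Working it through.** **1. The plan's own figure.** *Sample size* gives 69 infants (8 + 61) for CP proportions of 50% and 5%, ratio 7.6:1, alpha 0.05, power 90%. The pooled two-sided formula is

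n₁ = [1.960·√(p̄q̄(1 + 1/k)) + 1.282·√(p₁q₁ + p₂q₂/k)]² / (p₁ − p₂)²

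with k = 7.6 and p̄ = (0.5 + 7.6 × 0.05)/8.6 = 0.102. This gives n₁ = 8.10 and a total of 8.10 × 8.6 ≈ 69.6. Power at 8 and 61 is 0.897. The figure reproduces, but it concerns CP by white matter group and says nothing about comparing predictors.

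**2. Each step set against the aim.**

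| Step described | Question it answers |
|---|---|
| Screen at p<0.15 | Does this variable differ from no effect? |
| Entry by significance | None; it sets the order |
| Likelihood ratio test | Does this variable add to those already in? |
| Effect estimates, 95% CI | How large is this effect? |
| Sensitivity, specificity | How accurate is the predictive model? |
| *Needed for the aim* | *How large is the difference between two predictors or blocks?* |

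No step supplies the last row.

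**3. One illustration (assumed values).** Take N = 80, observed correlations with the outcome of 0.4 and 0.3, and a correlation of 0.5 between the predictors. The univariable p-values are about 0.0002 and 0.007, so both pass the screen.

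- First entry: −80·ln(1 − 0.16) = 13.9, kept.
- Joint R² = (0.16 + 0.09 − 2 × 0.4 × 0.3 × 0.5)/(1 − 0.25) = 0.173.
- Second entry: 80·ln(0.84/0.827) = 1.28, below 3.84, so dropped.
- Williams test of equal dependent correlations: t = 0.96 on 77 df, p = 0.34.

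Selection keeps one predictor and drops the other, although the data do not distinguish them.

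**4. Simulation under equality.** Two predictors have the same true correlation r with one continuous outcome and correlation ρ with each other. There were 20,000 runs per cell. The described procedure was applied with an assumed likelihood ratio level of 0.05. N = 80 is the stated target; N = 64 is 80 less 20% attrition, should 80 be the number enrolled. Share of runs that keep exactly one predictor:

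| N | r | ρ = 0 | ρ = 0.3 | ρ = 0.5 |
|---|---|---|---|---|
| 80 | 0.2 | 49% | 60% | 60% |
| 80 | 0.3 | 29% | 66% | 83% |
| 80 | 0.4 | 4% | 30% | 66% |
| 80 | 0.5 | 0.1% | 4% | 26% |
| 64 | 0.2 | 46% | 53% | 53% |
| 64 | 0.3 | 39% | 70% | 80% |
| 64 | 0.4 | 9% | 44% | 76% |
| 64 | 0.5 | 0.4% | 11% | 42% |

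For r = 0.3–0.4 and ρ = 0.3–0.5 the range is about 30–84% across repeated simulations. With a likelihood ratio level of 0.10 it is about 19–80%, and with 0.15 about 13–76%. The Williams test declares a difference in about 5% of runs in every cell.

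**5. What a direct comparison can resolve.** At ρ = 0.3 the 95% half-width for r₁ − r₂ is about 0.21–0.26 (N = 80) or 0.24–0.29 (N = 64). Power to separate 0.4 from 0.2 is 37% or 29%; for 0.5 against 0.2 it is 71% or 61%.

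**6. Choice of R².** Nutrition is four measures (protein, lipid, carbohydrate, energy). With four nutrition variables, three of them assumed to be noise, set against one risk factor of equal true R² at N = 80, a bootstrap interval on raw R² falsely favoured nutrition in 11–18% of runs in one simulation and 12–13% in another. With adjusted R² it was 4–6%.

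**7. CP cases expected.** 8 × 0.5 + 61 × 0.05 = 7.05, so about 7 in 69 infants.

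**The case against.** The strongest reply is that the article never says the comparison will be read from p-value order or from which variables survive. A reader might infer that it is decided that way, but the text has no such rule, and a fuller plan might specify a contrast. This stands, and the point must not be put as if the article prescribed a ranking by significance.

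It follows that the retention rates are not false-claim rates. Keeping one variable is not the same as declaring it superior, so setting 30–84% beside 5% is meaningful only if selection is used as the comparison. The rates also rest on r, ρ and a likelihood ratio level that the article does not give, and they fall below 1% for strong uncorrelated predictors.

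Other analyses are also described: covariables included when appropriate, separate EEG network methods, and voxel and region-of-interest imaging analyses. Not every component passes through the stepwise scheme. The second comparative statement is Discussion prose, and none of the four hypotheses ranks predictors. These points narrow the concern mainly to the last secondary aim.

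What does not stand is that this is only detail left to another document. The article commits to a specific model-building rule, and that rule cannot answer the comparative question it sets.

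**Conclusion.** The point holds in limited form. The last secondary aim is comparative, and the only model-building analysis described estimates no difference between predictors, so it cannot support a statement that one is more predictive. The same applies to the Discussion's promise, with less weight. This conclusion comes from reading the steps and needs no simulation.

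The size is conditional. *If* the answer were taken from selection, one of two equally good predictors would be kept alone in about 30–84% of studies. That assumes n = 64–80, r = 0.3–0.4, ρ = 0.3–0.5, a likelihood ratio level of 0.05, two single predictors, one continuous outcome and no missing data. Outside that range it can be negligible. For binary outcomes the argument is structural and has not been quantified. The change should be made, but it does not undermine the study's non-comparative aims.

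**What to change.** For the last secondary aim, fit the nutrition block and the competing risk-factor model or models in the same infants, whatever their univariable p-values. Report the paired difference in adjusted or optimism-corrected R² (bootstrap or cross-validated) with a 95% CI. Raw R² should not be used, because it favours the block with more variables. Even with adjusted R², the 4–6% in the simulation exceeds the nominal 2.5% in one direction, so the interval's behaviour should be checked for the actual block sizes.

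For binary outcomes, report the paired difference in optimism-corrected AUC with its CI, and state in advance that it will be wide for CP, with about 7 cases expected.

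Describe a predictor as more predictive or most accurate only when the CI for the difference excludes zero. Otherwise report the predictors as not distinguished. The alternative is to reword the aim and the Discussion sentence as non-comparative.

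The cost is a few sentences and a little more analysis, with no new data. The downside is that fewer superiority statements will be possible at this sample size.
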